## 11.6 Dose formulation analysis

One sample of resuspended drug product for viable count analysis will be taken at visits specified in Table 8.1-1 and Table 8.1-2. The samples will be sent for analysis to [REDACTED] on the same day as they were taken.

## 11.7 Safety assessments

### 11.7.1 *Adverse events*

The Principal Investigator is responsible for ensuring that all medical staff involved in the study is familiar with the content of this section and the content of the [REDACTED] standard operating procedures (SOPs) regarding emergencies and FIH studies.

#### 11.7.1.1 *Definition of adverse event*

An AE is any untoward medical occurrence in a clinical study subject administered a pharmaceutical product and which does not necessarily have a causal relationship with this treatment. An AE can therefore be any unfavorable and unintended sign (including clinically significant abnormal values from relevant tests, such as clinical safety laboratory tests, ECGs, vital signs), symptom, or disease temporally associated with the use of an IMP, regardless of whether it is considered related to the IMP.

Local bleeding and mild, transient inflammation in the wound area are common and expected reactions following skin biopsy. Therefore, bleeding and/or mild, transient inflammation observed during the early local tolerability evaluations, and when judged by the Investigator to be caused by a study procedure performed pre-treatment (i.e. due to biopsy) is reported as procedure-related in the eCRF. Bleeding, inflammation and infection assessed as non-procedure related will be reported as AEs.

#### 11.7.1.2 *Definition of serious adverse event*

An SAE is any AE that:

- results in death
- is life-threatening (this refers to an event in which the subject was at risk of death at the time of the event; it does not refer to an event that hypothetically might have caused death had it been more severe)
- requires inpatient hospitalization or prolongation of existing hospitalization
- results in persistent or significant disability/incapacity
- is a congenital anomaly/birth defect
- is medically important (this refers to an event that may not be immediately life-threatening or result in death or hospitalization, but may jeopardize the subject or may require intervention to prevent any of the SAEs defined above)

Examples of medically important events are intensive treatment in an emergency room for allergic bronchospasm or blood dyscrasias, convulsions that do not result in hospitalization, development of drug dependency, and drug abuse.

Planned hospitalizations or surgical interventions for a condition that existed before the subject signed the ICF and that did not change in intensity are not SAEs.

If there is any doubt as to whether an AE meets the definition of an SAE, a conservative viewpoint must be taken, and the AE must be reported as an SAE.

#### *11.7.1.3 Definition of adverse drug reaction*

The term adverse drug reaction (ADR) is to be used whenever either the Investigator or Sponsor or designee assessed the SAE as at least possibly related to the IMP.

#### *11.7.1.4 Definition of serious adverse drug reaction*

The term SADR is to be used whenever either the Investigator or Sponsor or designee assessed the SAE as at least possibly related to the IMP.

#### *11.7.1.5 Definition of suspected unexpected serious adverse reaction*

A SUSAR is any SADR whose nature or intensity is not consistent with the current version of the IB.

#### *11.7.1.6 Time period and frequency for collecting adverse events*

AEs (including SAEs) will be collected from the start of IMP administration until the end-of-study visit. From Visit 7 and 14 in the SAD and MAD part, respectively, pre-defined AEs will be asked for.

Any AE with start date on the day of first IMP administration must be recorded with start time.

At the end-of-study visit, information on new AEs, if any, and stop dates for previously reported AEs must be recorded (if known).

Investigators are not obligated to actively seek AE or SAE after conclusion of the study participation. However, if the investigator learns of any SAE, including a death, at any time after a participant has been discharged from the study, and he/she considers the event to be reasonably related to the study intervention or study participation, the investigator must promptly notify the sponsor.

#### *11.7.1.7 Assessment of severity/intensity*

The grading of the severity/intensity of AEs will follow the CTCAE v5.0. Grade refers to the severity of the AE. The CTCAE displays Grades 1 through 5 with unique clinical descriptions of severity for each AE based on this general guideline.

The Investigator must assess the severity/intensity of an AE using the following definitions, and record it on the AE Log in the eCRF:

|                |                                                                                                                                           |
|----------------|-------------------------------------------------------------------------------------------------------------------------------------------|
| Grade 1 | Mild; asymptomatic or mild symptoms; clinical or diagnostic observations only; intervention not indicated.                                |
| Grade 2 | Moderate; minimal, local or non-invasive intervention indicated; limiting age-appropriate instrumental activities of daily living (ADL)*. |

|                |                                                                                                                                                                           |
|----------------|---------------------------------------------------------------------------------------------------------------------------------------------------------------------------|
| Grade 3 | Severe or medically significant but not immediately life-threatening; hospitalization or prolongation of hospitalization indicated; disabling; limiting self- care ADL**. |
| Grade 4 | Life-threatening consequences; urgent intervention indicated.                                                                                                             |
| Grade 5 | Death related to AE.                                                                                                                                                      |

*\*Instrumental ADL refers to preparing meals, shopping for groceries or clothes, using the telephone, managing money, etc.*

*\*\*Self- care ADL refers to bathing, dressing and undressing, feeding self, using the toilet, taking medications, and not bedridden.*

#### 11.7.1.8 Assessment of causal relationship

The Investigator must assess the causal relationship between an AE and the IMP using the definitions below and record it in the AE Log of the eCRF:

- *Unlikely* – the AE has no temporal relationship to the IMP or is due to underlying/concurrent illness or effect of another drug (that is, there is no causal relationship between the IMP and the AE).
- *Possible* – the AE has a suggestive temporal relationship to the IMP, and an alternative etiology is equally or less likely
- *Probable* – the AE has a strong temporal relationship to the IMP or recurs on re-challenge, and another etiology is unlikely or significantly less likely

An AE is considered causally related to the use of the IMP when the causality assessment is *probable* or *possible*.

#### 11.7.1.9 Assessment of outcome

The Investigator must assess the outcome of an AE using the definitions below and record it on the AE Log of the eCRF:

- *Recovered/Resolved* – the subject has recovered completely, and no symptoms remain.
- *Recovering/resolving* – the subject's condition is improving, but symptoms still remain.
- *Recovered/resolved with sequelae* – the subject has recovered, but some symptoms remain (for example, the subject had a stroke and is functioning normally, but has some motor impairment).
- *Not recovered/not resolved* – the subject's condition has not improved, and the symptoms are unchanged (for example, an atrial fibrillation has become chronic).
- *Fatal*
- *Unknown*

#### *11.7.1.10 Collecting adverse events*

AEs identified using any of the following methods will be recorded:

- AEs spontaneously reported by the subject
- AEs observed by the Investigator or medical personnel
- AEs elicited based on non-leading questions from the Investigator or medical personnel

#### *11.7.1.11 Recording adverse events*

AEs must be recorded in the AE Log of the eCRF. The investigator must provide information on the AE, preferably with a diagnosis or at least with signs and symptoms; start and stop dates, start and stop time; intensity; causal relationship to IMP; action taken, and outcome.

If the AE is serious, this must be indicated in the eCRF (see Section 11.7.1.12).

AEs, including out-of-range clinically significant clinical safety laboratory values, must be recorded individually, except when considered manifestations of the same medical condition or disease state; in such cases, they must be recorded under a single diagnosis.

If the severity/intensity of an AE increases, the maximum intensity is recorded in the eCRF.

#### *11.7.1.12 Reporting of serious adverse events*

SAE reporting should be performed by the investigator within 24 hours of awareness via the eCRF. All available information regarding the SAE should be entered in the AE Log for the specific subject. By saving the event as “serious” in the eCRF, an e-mail alert is sent to predefined recipients to highlight that an SAE has been registered. The same information is automatically sent to [REDACTED]

The SAE report is reviewed by a designated person at [REDACTED] PV department to ensure that the report is valid and correct. For fatal or life-threatening SAEs where important or relevant information is missing, immediate follow-up is undertaken and queries to the site are raised. Investigators or other site personnel should inform [REDACTED] PV of any follow-up information on a previously reported SAE immediately but no later than the end of the next business day of when he or she becomes aware of it.

If the SAE report in the eCRF is updated, a new e-mail alert is sent to the predefined recipients.

The appointed Medical Monitor will provide his/her causality assessment and make an expectedness assessment once the report is judged to be complete. The reference document for definition of expectedness is the Reference Safety Information (RSI) in the current version of IB.

If any additional documentation is required (e.g. autopsy report), [REDACTED] PV will request this information from the study site.

In case the eCRF cannot be accessed, the SAE should be reported by manually completing the paper SAE Form, provided in the Investigator Site File (ISF). The completed, signed and dated paper SAE Form should, within 24 hours, be scanned or e-mailed to:

A copy of the paper SAE form must also be e-mailed to [REDACTED]

The study site should notify the site Monitor via phone or e-mail about the submission of the SAE report. As soon as the site personnel have access to [REDACTED] the SAE should be reported electronically as well.

The Sponsor has delegated to [REDACTED] the reporting of SAEs to competent authority (CA) and the independent ethics committee (IEC) in accordance with local regulations.

#### *11.7.1.13 Reporting of SUSARs to EudraVigilance, local CA and IEC*

The term SADR is used whenever either the investigator or medical monitor deems a blinded SAE as possibly or probably related to IMP. If an SADR is assessed as unexpected by the medical monitor, it is a potential SUSAR and under such circumstances an EudraVigilance reporter will be unblinded. In case the subject had received active treatment, the event is regarded as a SUSAR and the certified EudraVigilance reporter will report the SUSAR to the CA, via the EudraVigilance database, and to the IEC in accordance with local regulations and [REDACTED] SOPs within the following timelines:

- 7 calendar days if fatal or life-threatening (follow-up information within an additional 8 days)
- 15 calendar days if non-fatal and non-life-threatening (follow-up information as soon as possible)

The clock for expedited initial reporting (Day 0) starts as soon as the Sponsor has received the information containing the minimum reporting criteria. The date should be documented on an acknowledgement of receipt.

The medical monitor is responsible for medical review of the SAE narrative in the Council for International Organizations of Medical Sciences (CIOMS) form (or equivalent) prior to expedited reporting.

The Sponsor or delegate is responsible for informing the Investigators concerned of relevant information about potential SUSARs (blinded data) that could adversely affect the safety of subjects.

The Sponsor or delegate is responsible for once a year throughout the clinical study (or on request), submit a safety report to the CA and the IEC taking into account all new available safety information received during the reporting period.

#### *11.7.1.14 Treatment and follow-up of adverse events*

Subjects with AEs that occur during the study must be treated according to daily clinical practice at the discretion of the Investigator.

AEs must be followed up until resolution or to the end-of-study visit, whichever comes first. At the end-of-study visit, information on new AEs, if any, and stop dates for previously reported AEs must be recorded (if known). AEs assessed as stable by the Investigator at the end-of-study visit will not have to be followed up until resolution.

It is the responsibility of the Investigator to follow up on all SAEs until the subject has recovered, stabilized, or recovered with sequelae, and to report to the Sponsor all relevant new information using the same procedures and timelines as those for the initial report. Relevant information includes discharge summaries, autopsy reports, and medical consultation.

#### *11.7.1.15 Procedures in case of pregnancy*

In case of pregnancy or suspicion of possible pregnancy of any female partners of male subjects, the study treatment must be stopped immediately, and the subject discontinued from participation in the study. Pregnancy itself is not regarded as an AE unless there is a suspicion that the IMP may have interfered with the effectiveness of the contraceptive medication. However, the outcome of all pregnancies (spontaneous miscarriage, elective termination, normal birth or congenital abnormality) must be followed up and documented even after the subject was discontinued from the study.

All events of congenital abnormalities/birth defects are SAEs. Spontaneous miscarriages should also be reported and handled as AEs. All outcomes of pregnancy must be reported to the Sponsor and the Principal Investigator on the pregnancy outcomes report form.

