#### **Duration of treatment**

**SAD part:** a single topical application of activated ILP100-DP to 2 wounds and placebo to 2 wounds

**MAD part:** 10 topical applications of activated ILP100-DP to 4 wounds, placebo to 2 wounds and saline to 2 wounds

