be checked as detailed in Table 8.1-2. There is immediate access to equipment, qualified staff and an ICU in case of an acute emergency. Up to 4 subjects will be dosed on the same day.

The wounds will be photographed in a standardized setting according to instructions specified in a separate manual, and briefly summarized in Section 11.5, before treatment on Day 1, pre-treatment at the subsequent dosing visits, and at all follow-up visits to the research clinic. Selected members of the clinical staff will receive photography training prior to handling of the camera equipment. In addition, wounds will be analyzed using a 3D camera as outlined in Section 11.9.1.

Following the first dose on Day 1, subjects will come for 10 additional visits between Day 2 and Day 21 (Visits 3 to 12). The last dose will be given on Day 19 (Visit 11). Safety will be assessed by vital signs, safety laboratory parameters, local tolerability, AEs, use of concomitant medications and CXCL12 ADA analysis at visits outlined in Table 8.1-2.

The wounds must not at any visit be cleaned (unless necessary for safety reasons, e.g. due to an infection). The area surrounding the wounds should then be carefully cleaned with water if necessary. At visits when swabbing is performed, the area around the wound should be cleaned after swabbing if necessary. Before the subject leaves the research clinic, the wound should be dressed until healed.

Blood sampling for analysis of CXCL12 and *L. reuteri* systemic levels and a swab of the area surrounding the wounds and feces sampling for analysis of any presence of *L. reuteri* R2LC colonies containing the pSIP411 plasmid will be performed at time points and visits specified in Table 8.1-2.

For exploratory purposes, microcirculation assessments will be performed and dressings will be collected at time points outlined in Table 8.1-2.

An end-of-treatment phase visit (Visit 13) will take place on Day 32 ( $\pm 1$  day) or after early withdrawal.

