## 8.2 Rationale for study design

The European Medicines Agency (EMA) guideline on strategies to identify and mitigate risks for FIH and early clinical trials with IMPs (EMA/CHMP/SWP/28367/07 Rev. 1) has been considered as have the European Directive 2001/18/EC on the deliberate release into the environment of GMOs and the guidance on the environmental risk assessment of genetically modified organisms from the EMA CHMP/GTWP/125491/06. A 5-year long-term follow-up has been included in line with the recommendations given in EMA/CHMP/GTWP/60436/2007.

The SAD/MAD design of the study is based on the aim to study safety, tolerability and exposure of selected doses of activated ILP100-DP in a limited number of healthy volunteers.

The design is adaptive to allow for flexible dose escalation and involves careful monitoring of the subject's well-being. The study will provide important safety and tolerability data and preliminary efficacy data to support the design of further studies, both in healthy volunteers and in patients.

A placebo control will be used to establish the frequency and magnitude of changes in endpoints that may occur in the absence of active treatment. Subjects will serve as his/her own control receiving both placebo and active treatment on the same occasion. The placebo component consist of the ILP100-DP dilution buffer and the activation peptide SppIP. The dilution buffer contains sucrose, which may have a wound healing effect. Recombinant CXCL12 is not used as placebo since the half-life is too short (approximately 6 seconds) to provide clinically relevant data (Laguri *et al.*, 2007; Lambeir *et al.*, 2001). *Lactobacillus* wild-type is not used as placebo since extensive testing in non-clinical studies have shown that it has no effect on wound healing.

Saline (0.9 % NaCl) will be used as a “no treatment” control for several purposes, 1) all wounds must be treated with a solution to keep the blind, 2) all wounds must be exposed to comparable moisture during the study since moisture is a parameter that affects wound healing and 3) NaCl will identify any wound healing properties of sucrose in the dilution buffer used for both ILP100-DP and placebo.

Randomization will be used to minimize bias in the assignment of treatments to wounds.

Blinded treatment will be used to reduce potential bias during data collection and evaluation of endpoints.

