## 9.4 Inclusion criteria

For inclusion in the study, subjects must fulfil the following criteria:

1. Willing and able to provide a written informed consent for participation in the study.
2. Healthy males and females aged  $\geq 25$  and  $\leq 45$  years.
3. Willing and able to comply with study requirements.
4. Non-obese subjects with a body Mass Index (BMI)  $\geq 18.0$  and  $\leq 30.0$  kg/m^2 and weight at least 50 kg and no more than 120 kg at screening.
5. Clinically normal medical history, physical findings, vital signs, ECG and laboratory values at the time of screening, as judged by the Investigator.
6. Women of child bearing potential (WOCBP) must agree to use a highly effective method of contraception with a failure rate of  $< 1\%$  to prevent pregnancy (combined [estrogen and progestogen containing] hormonal contraception associated with inhibition of ovulation [oral, intravaginal, transdermal], progestogen-only hormonal contraception associated with inhibition of ovulation [oral, injectable, implantable], intrauterine device [IUD] or intrauterine hormone-releasing system [IUS]) from at least 4 weeks prior to dose until 3 months after the last dose of IMP and until confirmation of negative 6 weeks skin swab and feces analyses concerning *L. reuteri* R2LC and/or pILP100 findings. Their male partner must agree to use a condom during the same time frame.

Women of non-childbearing potential are defined as pre-menopausal females who are sterilized (tubal ligation or permanent bilateral occlusion of fallopian tubes); or post-menopausal defined as 12 months of amenorrhea (in questionable cases a blood sample with simultaneous detection of follicle stimulating hormone [FSH] 25-140 IE/L and estradiol  $< 183$  pmol/l is confirmatory).

Male subjects must be willing to use condom or be vasectomized to prevent pregnancy and drug exposure of a partner and refrain from donating sperm from the date of dosing until 3 months after the last dose of IMP and until confirmation of negative 6 weeks skin swab and feces analyses concerning *L. reuteri* R2LC and/or pILP100 findings. Their female partner of child-bearing potential must use contraceptive methods with a failure rate of  $< 1\%$  to prevent pregnancy (see above).

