## 9.6 Restrictions during the study

The subjects must be willing to comply with the following restrictions during the entire study duration *i.e.*, from screening to the Visit 6 of the SAD part and Visit 13 of the MAD part unless otherwise stated below.

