### 9.6.1 General restrictions

- Contraception Requirements: The male volunteers are expected to use condom to prevent pregnancy and drug exposure of a female partner and refrain from donating sperm from the date of the first dose until 3 months after the last dose of IMP and until confirmation of negative 6 weeks skin swab and feces analyses concerning *L. reuteri* R2LC and/or pILP100 findings. In addition, they need to ensure that their fertile female partners should use contraceptive methods with a failure rate of < 1% to prevent pregnancy (for details, refer to inclusion criterion No 6). The female volunteers are expected to use a contraceptive method with a failure rate of < 1% to prevent pregnancy (for details, refer to inclusion criterion No 6). Abstinence alone is not defined as a highly effective prevention for men or WOCBP.
- Alcohol: Consumption of alcohol is not allowed within 48 hours prior to all visits to the clinic including the end-of-study visit and during visits at the research clinic.  
In addition, in the MAD, consumption of alcohol is disallowed from the first dose until the subjects leave the research clinic after the last dose.
- Nicotine: Smoking or use of nicotine-containing products is not allowed during the study (from screening to Visit 6 in the SAD part and Visit 13 in the MAD part).

- Xanthine or taurine containing products/beverages: Energy drinks (e.g. Redbull) are not allowed during the study (from screening to Visit 6 in the SAD part and Visit 13 in the MAD part).
- Coffee: Not more than 5 cups of coffee per day will be allowed during the study (from screening to Visit 6 in the SAD part and Visit 13 in the MAD part).
- Blood donation, blood components and organs: The subjects must not donate blood, plasma, other blood components or any organs during the study until 3 months after the last dose of IMP and until confirmation of negative 6 weeks skin swab and feces analyses concerning *L. reutrei* R2LC and/or pILP100 findings.
- Participation in other clinical studies: Study subjects are not allowed to participate in any other clinical study during the study period until 3 months after the last dose of IMP and until confirmation of negative 6 weeks skin swab and feces analyses concerning *L. reuteri* R2LC and/or pILP100 findings.
- Activity: study subjects will abstain from strenuous exercise for 72 hours before each blood collection for clinical laboratory tests.

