### 9.8.2 *Procedures for discontinuation of a subject from the study*

A subject who prematurely discontinues participation in the study will always be asked about the reason(s) for discontinuation and the presence of any AEs. If a subject withdraws consent,

the investigator must ask the subject if he/she is willing, as soon as possible, to be assessed according to the procedures scheduled for Visit 6 and Visit 13 visit in each part. Any ongoing AEs will be followed as described in Section 11.7.1.14.

The primary reason for discontinuation/early withdrawal must be specified in the end-of-treatment form of the eCRF and final drug accountability must be performed.

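### The pregnancy rule in Section 11.7.1.15 has no end date and ties stopping IMP to leaving the study, so read literally it removes men from the 5-year safety follow-up after dosing is over

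*Protocol*

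**What the plan says.** Section 11.7.1.15 makes two actions mandatory in one sentence. On pregnancy, or suspected pregnancy, the protocol says of "pregnancy of any female partners of male subjects, the study treatment must be stopped immediately, and the subject discontinued from participation in the study". It sets no time limit and makes no exception for men who have finished dosing. What it keeps going after discontinuation is the follow-up of the pregnancy outcome, not the subject's own safety visits.

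The contraception duty, by contrast, has an end. Section 9.6.1 applies it to male volunteers "until 3 months after the last dose of IMP and until confirmation of negative 6 weeks skin swab and feces analyses". Inclusion criterion 6 in Section 9.4 uses the same limit, asking men to "refrain from donating sperm from the date of dosing until 3 months after the last dose of IMP".

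Dosing ends early. The synopsis describes the SAD treatment as "a single topical application of activated ILP100-DP to 2 wounds and placebo to 2 wounds", given on Day 1 (Visit 2). Section 8.1.2 places the last MAD dose on Day 19 (Visit 11).

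The long follow-up has a stated purpose. Section 8.2 says: "A 5-year long-term follow-up has been included in line with the recommendations given in EMA/CHMP/GTWP/60436/2007". Sections 8.1.1 and 8.1.2 count these 5 years as part of each subject's participation, and Section 15.6 ends the study at the last subject's last visit. Section 9.8.2.1 foresees withdrawals after Visit 6 (SAD) or Visit 13 (MAD) and rules out replacing those subjects.

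**The concern.** Stopping treatment and leaving the study are different acts, and the sentence joins them. While doses remain, or within the contraception window, stopping IMP has a reason: a partner should not be exposed to the product. After the window, discontinuation protects neither the partner nor the subject. Its only effect is to end collection of the man's anti-drug antibody (ADA), swab, feces, scar and adverse event data.

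Those are the data for which a 5-year follow-up of a gene therapy product was planned. Adverse events and ADA are also primary endpoints. The cohorts are small, so one man is 1 of 4 in a SAD cohort or 1 of 8 in a MAD cohort. The trigger includes mere suspicion, and the section gives no way back if the suspicion proves wrong.

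**Working it through.** The protocol gives no figure to reproduce here. The check compares sections and counts visits.

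**1. Does the rule reach past the contraception window?** Section 11.7.1.15 has no end date. Section 9.4 (criterion 6) and Section 9.6.1 end the duty at 3 months after the last dose, provided the 6-week samples are negative. A partner's pregnancy in, say, year 3 therefore breaches nothing but still falls under the literal wording.

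**2. Does leaving participation mean leaving the 5-year follow-up?** Sections 8.1.1 and 8.1.2 describe participation as the first phase plus 5 years. Section 15.6 runs the study to the last follow-up visit, and Section 9.8.2.1 treats withdrawal during follow-up as possible. On these sections the answer is yes.

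**3. When is there no treatment left to stop?**
- SAD: the only dose is at Visit 2 and the last visit is Visit 14. Visits after the last dose: 14 − 2 = 12 (Visits 3 to 14).
- MAD: the last dose is at Visit 11 and the last visit is Visit 21. Visits after the last dose: 21 − 11 = 10 (Visits 12 to 21).

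For every treated SAD man the treatment half of the sentence is empty, and discontinuation is the rule's only effect. These counts include visits inside the contraception window, so they do not measure the loss after it. Step 4 does.

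**4. What is lost per event?** From Tables 8.1-1 and 8.1-2, the same in both parts:
- Long-term visits: 6 weeks, 3, 6 and 12 months, years 2, 3, 4 and 5 = 8.
- Long-term ADA, swab and feces samplings: 6 weeks, 12 months, years 2, 3, 4 and 5 = 6.

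| Discontinued just after | Visits lost | Samplings lost |
|---|---|---|
| 3 months | 8 − 2 = 6 of 8 | 6 − 1 = 5 of 6 |
| 12 months | 8 − 4 = 4 of 8 | 6 − 2 = 4 of 6 |
| Year 4 | 8 − 7 = 1 of 8 | 6 − 5 = 1 of 6 |

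In time, about 60 − 3 = 57 of 60 follow-up months (57/60 = 95%) lie after the window. This assumes that the 6-week samples are confirmed negative by month 3.

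**5. How often?** This cannot be derived. Pregnancy tests are for female subjects only (Section 11.3.8) and no partner test is scheduled, so a late partner pregnancy would reach the site mainly if the subject volunteers it. Subjects are 25 to 45 years old at entry, which makes such an event plausible over 5 years, but no more can be said.

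**The case against.** The best counter-argument is that the sentence is meant for the dosing period. It speaks of stopping treatment, which presupposes treatment under way, and the text that follows it refers to contraceptive medication. Section 9.6 describes the study duration for its restrictions as "from screening to the Visit 6 of the SAD part and Visit 13 of the MAD part". Section 9.8.2 handles discontinuation with treatment-phase steps: "The primary reason for discontinuation/early withdrawal must be specified in the end-of-treatment form of the eCRF". Section 9.8.1 does not list pregnancy among the withdrawal reasons, and Section 15.6 separates completing the treatment phase from completing the follow-up. On this view nothing says that a pregnancy in year 3 removes anyone.

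That reading is possible, and the sponsor may well have intended it. The text does not secure it. Section 9.6 governs only the restrictions. The form in Section 9.8.2 is where a reason is recorded and does not limit when the pregnancy rule applies. In the SAD part the dosing-period reading would leave the rule almost nothing to act on.

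It is also fair that the loss is bounded. Data already collected stay in the full analysis set. Serious adverse events are followed until recovery or stabilization (Section 11.7.1.14), and related serious events learned of later must still be notified (Section 11.7.1.6). The long-term data are summarized descriptively, and there is no formal sample size to erode. These points limit the weight of the concern but do not remove it.

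**Conclusion.** The concern holds. Section 11.7.1.15 is a mandatory rule without an end date that does not separate stopping IMP from leaving follow-up. Followed as written, it costs up to 6 of 8 long-term visits and 5 of 6 long-term samplings for a man whose partner's pregnancy becomes known after the contraception window, and the loss shrinks the later this happens.

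The conclusion rests on the literal wording and on participation including the 5 years; the sponsor's intention cannot be read from the protocol, and the frequency is unknown. No endpoint definition, estimate or escalation decision changes. This is a cheap improvement that should be made, not a design error.

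**What to change.** Reword Section 11.7.1.15 so that pregnancy of a female subject, or of a male subject's partner within the contraception window of inclusion criterion 6, stops any remaining IMP and nothing else. State that the subject stays in long-term follow-up in all cases, subject to the right to withdraw in Section 9.8.1. Allow individual procedures to be postponed during a subject's own pregnancy. Keep the outcome follow-up of all pregnancies.

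In the same edit, name female subjects explicitly, because the present discontinuation sentence mentions only partners, and add a cross-reference in Section 9.8.1.

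The cost is the rewording of one section and one cross-reference in a protocol amendment. It adds no visits, samples or subjects. The small downside is that some follow-up procedures may be delayed during a subject's own pregnancy.
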